### Sample Size and Power Calculation

Based on preliminary data from our institution’s EHR, it was determined that there would be a maximum of 1400 participants in the practice who could meet inclusion criteria. The study was powered for the clinical outcome of BP change, with calculations performed using the clustersampsi command for Stata version 11.2. We assumed a 2-tailed alpha level of 0.05, an intraclass correlation coefficient of 0.025 based on studies in primary care settings [49,50], and a standard deviation of 5 mmHg. Assuming 23 clinicians per arm with at least 15 patients per clinician (ie, 345 patients per arm), we estimated that we would have 80% power to detect a difference as small as 1.27 mmHg between arms.

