#### Recruitment Rate

At the provider level, all 81 eligible PCPs (47 faculty attending physicians, 31 resident physicians, and 3 NPs) agreed to participate (100%). In total, 79 of the 81 providers (98%) were included because 2 providers had no remaining eligible participants after exclusion and opt-outs. At the patient level, 995 patients who met the initial eligibility criteria were identified. A total of 316 / 995 (31.8%) potential patient participants were excluded using automated algorithms, and clinicians excluded another 90 patients (Figure 1). A total of 582 patient participants were distributed to the 3 arms based on provider randomization. After an additional 3 patients were excluded (owing to patient deaths not recorded in EHR before randomization) and 55 / 582 patients (9.5%) opted out or withdrew, 524 patient participants (90.0% of eligible 582 participants) were included in the study: 188 usual care, 165 eCDSS, and 171 eCDSS+.

Baseline patient participant characteristics are shown in Table 1. The 55 patients that opted out/withdrew were similar to the patient participants across multiple traits—including age, gender, race/ethnicity, language preference, and co-morbidities—except they had lower renal function on average: eGFR_Cr_ (52.7 [SD 11.7] versus 56.0 [SD 11.8]; *P*=.046).

**Table 1 table1:** Baseline characteristics of all included patients (N=524).

Patient characteristic		Values
Age (years), mean (SD)		70.3 (8.9)
Female, n (%)		236 (45)

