### Limitations

As a pilot study, this study was limited by its inclusion of patients and providers from a single institution. Therefore, both the intervention and strategies to encourage intervention uptake were adapted to meet the needs of this single institution that uses Epic Systems’ EHR. However, we have found that the patient population in this clinic is similar to others [60], and Epic is a widely used EHR in multiple health systems. As a pragmatic trial, our sample size was smaller than initially anticipated and will thus ultimately impact our power to detect changes in our primary outcome. The short follow-up period for this pilot study will also limit our ability to assess some clinical outcomes. However, we were still able to use this pilot study to determine the feasibility of this intervention.

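### The planned 80% power for 1.27 mmHg does not describe the trial as conducted: the size was not reached, and the unsourced 5 mmHg SD is implausibly small for systolic BP

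*Protocol article*

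**What the plan says.** All the places are in the Protocol article.

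- **Sample Size and Power Calculation.** "The study was powered for the clinical outcome of BP change". The inputs are "We assumed a 2-tailed alpha level of 0.05", "an intraclass correlation coefficient of 0.025 based on studies in primary care settings" and "a standard deviation of 5 mmHg. Assuming 23 clinicians per arm with at least 15 patients per clinician (ie, 345 patients per arm". The result is "80% power to detect a difference as small as 1.27 mmHg between arms". The ICC carries references. The SD carries none and is not labelled systolic or diastolic.
- **Primary Outcome.** Systolic and diastolic change from baseline are analysed separately.
- **Recruitment Rate.** 79 providers remained, and the patients "were included in the study: 188 usual care, 165 eCDSS, and 171 eCDSS"+.
- **Table 1.** Baseline quartiles are 117 to 140 mm Hg for SBP and 62.5 to 75 mm Hg for DBP.
- **Limitations.** "our sample size was smaller than initially anticipated and will thus ultimately impact our power to detect changes in our primary outcome". No revised figure follows, and the SD is not mentioned.

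**The concern.** The power statement is the only place where the article says how small a BP effect the trial could detect. Two of its inputs do not fit what the same article reports: about half the assumed patients were included, and an SD of 5 mmHg sits beside a systolic interquartile range of 23 mmHg. If the change SD is much larger than 5, a null BP result leaves differences of several mmHg open, while a reader holding on to 1.27 mmHg would think them excluded. The Limitations section points only to sample size, which is the smaller of the two effects.

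**Working it through.** **1. Reproducing the planned figure.** Inputs from the sample size section: k = 23 clinicians per arm, m = 15, n = 345 per arm, ICC = 0.025, SD = 5, two-sided alpha 0.05, power 80%.

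- Design effect: 1 + (15 − 1) × 0.025 = 1.35
- Standard error: 5 × √(1.35 × 2/345) = 0.442
- Degrees of freedom: 2 × (23 − 1) = 44, so the t quantiles sum to 2.015 + 0.850 = 2.865
- Detectable difference: 2.865 × 0.442 = 1.267 mmHg

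This matches 1.27. Normal quantiles give 1.24.

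**2. Achieved size, SD kept at 5.** Usual care (188) against eCDSS (165), with mean cluster size 524/79 = 6.63. About 26.3 PCPs per arm (79/3, an even split assumed) gives roughly 50 degrees of freedom and t quantiles summing to 2.857. Design effect = 1 + ((CV² + 1) × m − 1) × ICC, where CV is the coefficient of variation of cluster size. The article's text does not give the CV, so 0 and 0.7 are taken as assumed bounds.

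| | CV 0 | CV 0.7 |
|---|---|---|
| Design effect | 1.14 | 1.22 |
| SE = 5 × √(DE × (1/188 + 1/165)) | 0.570 | 0.590 |
| Detectable difference (mmHg) | 1.63 | 1.68 |
| Power for 1.27 mmHg (noncentral t) | 59% | 56% |

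The loss is limited partly because there are more clusters than planned (79 against 3 × 23 = 69) and they are smaller, which lowers the design effect.

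**3. What Table 1 implies for the SD.** Under a normal approximation, SD = IQR/1.349.

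- SBP: 23/1.349 = 17.05
- DBP: 12.5/1.349 = 9.27

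With equal spread at both times, the change SD is SD₀ × √(2(1 − r)), where r is the baseline to follow-up correlation. Setting this to 5 and solving:

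- SBP: r = 1 − 25/(2 × 17.05²) = 0.957
- DBP: r = 1 − 25/(2 × 9.27²) = 0.854

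Adjusting for baseline hardly helps. A residual SD of 5 from SD₀ × √(1 − r²) needs r of about 0.956 and 0.842.

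**4. Detectable difference at the achieved size with a change SD from Table 1.** The correlation is not in the article, so a range is shown. Each pair of figures is CV 0 to CV 0.7.

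| r (assumed) | SBP change SD | SBP detectable (mmHg) | DBP change SD | DBP detectable (mmHg) |
|---|---|---|---|---|
| 0.4 | 18.68 | 6.08–6.29 | 10.15 | 3.30–3.42 |
| 0.5 | 17.05 | 5.55–5.75 | 9.27 | 3.02–3.12 |
| 0.6 | 15.25 | 4.96–5.14 | 8.29 | 2.70–2.79 |
| 0.7 | 13.21 | 4.30–4.45 | 7.18 | 2.34–2.42 |
| 0.8 | 10.78 | 3.51–3.63 | 5.86 | 1.91–1.97 |
| 0.9 | 7.62 | 2.48–2.57 | 4.14 | 1.35–1.40 |

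Baseline-adjusted analysis at r = 0.4 to 0.7 gives about 4.0 to 5.3 for SBP and 2.1 to 2.9 for DBP. At SBP change SD 17 (r = 0.5), power for 1.27 mmHg is about 10%.

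**5. Which input matters more.** Size alone moves 1.27 to 1.63, a factor of 1.28. For SBP at r = 0.5, the SD alone multiplies the figure by 17.05/5 = 3.41. Even the full planned 345 per arm would then detect only about 4.3 mmHg.

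**The case against.** The strongest reply has four parts.

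- **Levels are not changes.** Table 1 gives the spread of baseline readings, whereas the calculation concerns change. A reader might infer that Table 1 contradicts the 5 mmHg SD outright. It does not: the step needs a correlation that the article never gives and a roughly normal shape, although Table 1 reports medians and quartiles. What stands is the conditional statement that 5 mmHg for SBP requires a correlation near 0.96. For DBP the requirement is 0.85, which is far less extreme.
- **The follow-up reading is not fully fixed.** Baseline is a single most recent reading, but all ambulatory readings are collected afterwards, and carrying the last one forward is tied to rates of control. If the continuous outcome averages several readings, its SD would be smaller. That argues for taking the SD from the trial's own data. It does not rescue an unsourced 5.
- **The shortfall is disclosed.** The power statement is prospective, the achieved numbers are reported, and the Limitations section says that power will suffer. This is correct, so the failure to reach the planned size is not a hidden fault. What is missing is a revised figure and any mention of the SD.
- **It was a planning calculation.** It should remain on record as the basis on which the trial was designed. That is right, and it shapes the fix.

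**Conclusion.** The statement of 80% power for 1.27 mmHg is arithmetically sound but is not a property of the trial as conducted. On the article's own SD and ICC, the achieved size gives a detectable difference of about 1.6 to 1.7 mmHg and 56 to 59% power for 1.27. The SD is the larger problem, chiefly for SBP. With a correlation of 0.4 to 0.7, the change-score detectable difference is about 4.3 to 6.3 mmHg for SBP and 2.3 to 3.4 mmHg for DBP. At 0.8 it is about 3.5 and 1.9.

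These figures rest on a normal approximation to the quartiles, equal spread at baseline and follow-up, ICC 0.025, cluster-size CV between 0 and 0.7, an even split of PCPs, and one pairwise comparison at two-sided 0.05.

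Two stronger readings are not supported. A reader might take 4 to 6 mmHg as the trial's true detectable difference. It applies to SBP only and depends on the assumed correlation. A reader might also scale that figure up because the BPA was opened for only 102 of 336 intervention patients, and conclude that an even larger effect is needed in those reached. That would require all benefit to pass through an opened BPA. The article describes other routes: the PCP training video, reminder emails, recommendations visible by hovering over the alert, and nephrologist contact with PCPs.

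**What to change.** Keep the 1.27 mmHg calculation, labelled as the planning calculation, and say which BP measure the 5 mmHg SD refers to and where it came from. State that it does not describe the trial as conducted. Add, for SBP and DBP separately, the difference detectable with 80% power at 188, 165 and 171 patients under 79 PCPs. Use the change or baseline-adjusted SD from the trial's own EHR readings and the actual variation in cluster size. Extend the Limitations sentence to cover the SD as well as the sample size.

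This is rewording plus one short calculation on data the team already holds. Design, outcomes and analysis stay as they are. The only downside is a less favourable stated figure.

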## Results

### Implementation Outcomes: Reach

Implementation outcomes at the end of the 12-month intervention period on October 4, 2018, are summarized below:

#### Recruitment Rate

At the provider level, all 81 eligible PCPs (47 faculty attending physicians, 31 resident physicians, and 3 NPs) agreed to participate (100%). In total, 79 of the 81 providers (98%) were included because 2 providers had no remaining eligible participants after exclusion and opt-outs. At the patient level, 995 patients who met the initial eligibility criteria were identified. A total of 316 / 995 (31.8%) potential patient participants were excluded using automated algorithms, and clinicians excluded another 90 patients (Figure 1). A total of 582 patient participants were distributed to the 3 arms based on provider randomization. After an additional 3 patients were excluded (owing to patient deaths not recorded in EHR before randomization) and 55 / 582 patients (9.5%) opted out or withdrew, 524 patient participants (90.0% of eligible 582 participants) were included in the study: 188 usual care, 165 eCDSS, and 171 eCDSS+.

Baseline patient participant characteristics are shown in Table 1. The 55 patients that opted out/withdrew were similar to the patient participants across multiple traits—including age, gender, race/ethnicity, language preference, and co-morbidities—except they had lower renal function on average: eGFR_Cr_ (52.7 [SD 11.7] versus 56.0 [SD 11.8]; *P*=.046).

**Table 1 table1:** Baseline characteristics of all included patients (N=524).

Patient characteristic		Values
Age (years), mean (SD)		70.3 (8.9)
Female, n (%)		236 (45)
**Race/ethnicity, n (%)**		
	White	277 (53)
	Asian	118 (23)
	Black/African American	70 (13)
	Hispanic	38 (7)
	Other	20 (4)
**Preferred language, n (%)**		
	English	469 (90)
	Chinese	39 (7)
	Spanish	16 (3)
**Insurance, n (%)**		
	Private insurance	146 (28)
	Medicare	215 (41)
	Medicaid	163 (31)
**Medical co-morbidities, n (%)**		
	Cerebrovascular disease	36 (7)
	Congestive heart failure	40 (8)
	Coronary artery disease	95 (18)
	Diabetes mellitus	199 (38)
	Hyperlipidemia	302 (58)
	Hypertension	377 (72)
**Medication use, n (%)**		
	Angiotensin converting enzyme inhibitor/angiotensin II receptor blocker	319 (61)
	Diuretic	199 (38)
	Statin	353 (67)
**CKD-related outcomes, n (%)**		
	Chronic kidney disease (CKD) on problem list	61 (12)
	CKD on problem list or primary care visit diagnosis by ICD-10^c^ codes	247 (47)
Systolic BP^a^ (mm Hg), median (Q1-Q3)		128 (117-140)
Diastolic BP (mm Hg), median (Q1-Q3)		68 (62.5-75)
BP controlled^b^ (<140/90), n (%)		373 (71)
Estimated glomerular filtration rate based by serum creatinine (mL/min), mean (SD)		56.0 (11.8)

^a^BP: blood pressure.

^b^BP control reported based on only the most recent measurement before the start of the study.

^c^ICD-10: International Classification of Diseases, Tenth Revision, Clinical Modification.

#### Completion of Triple Marker

Of the 336 patient participants in the intervention arms, 178 (53.0%) completed the triple-marker screening.

#### PCP Visits

Of the 178 patient participants who completed a triple-marker screen, 138 (77.5%) had a PCP visit during the 12-month intervention period. This was 41.1% (138/336) of all intervention participants.

#### PCP BPA Use

Of the 138 participants with a PCP visit, the BPA was opened for 102 participants (73.9%). This was 30.3% (102/336) of all intervention participants.

### Implementation Outcomes: Adoption

#### SmartSet Use

Of the 102 participants in which the BPA was opened, orders were signed or patient education was given from the SmartSet for 83 participants (81.4%).

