**Results:**

A multidisciplinary team (primary care internist, nephrologists, pharmacist, and informaticist) designed the eCDSS to integrate into the current clinical workflow. All 81 PCPs contacted agreed to participate and were randomized. Of 995 patients initially eligible by eGFR_Cr_, 413 were excluded per protocol and 58 opted out or withdrew, resulting in 524 patient participants (188 usual care; 165 eCDSS; and 171 eCDSS+). During the 12-month intervention period, 53.0% (178/336) of intervention patient participants completed triple-marker labs. Among these, 138/178 (77.5%) had a PCP appointment after the triple-marker labs resulted; the eCDSS was opened for 73.9% (102/138), with orders or education signed for 81.4% (83/102).

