### Intervention

Before the eCDSS rollout but after randomization, all participating PCPs randomized to an intervention arm were asked to watch an educational video that provided background on guideline-based CKD care, as well as information on what to expect when an enrolled patient participant came in for a visit. PCPs were given an incentive of US $10 and a chocolate bar upon watching the video. Overall, 69.8% (72.0% eCDSS and 67.9% eCDSS+) viewed the video.

Before the eCDSS rollout, between October 5, 2017 and October 12, 2017, one of the study investigators (LK) ordered triple-marker testing for each patient participant from the eCDSS arm (n=169) and each patient participant from the eCDSS+ arm (n=177). We excluded 48 patients who opted out. In total, 10 patients withdrew later.

After the triple-marker testing was ordered, the next time the patient participant visited the lab for their regular clinical care, the triple-marker labs were also collected. We programmed the eCDSS to trigger the first time that the patient participant visited their PCP after all 3 lab results were available. (see Figure 2 for the study workflow) The eCDSS best practice advisory (BPA) appeared above the current medications in the electronic chart (Figures 3 and 4). PCPs could choose to open the BPA by clicking an “accept” button. We also allowed PCPs to view the recommendations by hovering over the BPA before accepting it. For patient participants categorized as low risk, when the PCP accepted the BPA, triple-marker labs with an expected completion date 6 months hence prepopulated were automatically pending for the PCP to sign. For patient participants categorized as high risk, when the PCP accepted the BPA, a SmartSet (EpicCare, Epic Systems) of tailored orders and recommendations appeared (Figure 5). If the PCP did not open the BPA and sign the orders in the SmartSet during the first PCP visit after the triple-marker labs were available, the BPA would trigger at up to 2 additional PCP visits during the study period. The eCDSS did not trigger if the patient participant saw a provider who was not their PCP.

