#### Secondary Outcomes

Our main secondary outcome is PCP awareness of the patient participant’s CKD diagnosis, as measured by inclusion of CKD-related International Statistical Classification of Diseases and Related Health Problems-10th Revision codes on the problem list or as a visit diagnosis. Additional secondary outcomes include process of care, patient-centered, and implementation outcomes.

There are 2 main process of care outcomes: (1) the proportion of patient participants with albuminuria prescribed ACEi/ARB and (2) appropriate use of statins. Appropriate statin use is defined both as the proportion of all patient participants aged ≥50 years prescribed statin therapy and the proportion of participants initiated on statin therapy after study start date.

Patient-centered outcomes include patient knowledge about CKD and NSAID avoidance as measured by patient surveys.

In addition to the effectiveness outcomes described above, the implementation outcomes are described in detail in Textbox 1 using the reach, effectiveness, adoption, implementation, and maintenance (or RE-AIM) framework to highlight measures crucial to successful implementation [47]. In this paper, we report initial implementation results, including all of the Reach outcomes and the first Adoption outcome (PCP SmartSet use).

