## Discussion

### Principal Findings

In this report, we describe the rationale, design, and initial implementation outcomes of a 3-arm pragmatic trial that assessed the feasibility and preliminary effectiveness of an eCDSS to improve CKD management in primary care compared with usual care. This study builds on previous pragmatic trials focused on EHR-based interventions to improve CKD management [28,29,51,52] and supports the feasibility of using EHRs to identify study participants, intervene in early CKD management, and measure study outcomes. Given its design as a pragmatic trial (per Pragmatic Explanatory Continuum Indicator Summary, or PRECIS, criteria [53]), we found high rates of participation by providers and low opt-out rates by patients. We also found high rates of eCDSS use by providers.

This study has many innovative components. We utilized a 3-armed trial design, which included a usual care group as well as a group with pharmacist-patient engagement after the provider-facing electronic intervention. In addition, our clinical eCDSS was mostly automated and individualized to patients based on laboratory results, rather than a generic CDSS for all participants. We also implemented the recommended triple-marker risk stratification approach to better characterize participants’ risk for CKD progression. Our participants included non-English speakers, who have been excluded from many other trials. This trial also included multiple types of outcomes allowing for a deeper understanding of the intervention’s impact on care processes. Reviews of eCDSS have found that few studies assess unintended consequences or adverse effects of a CDSS, which can be widespread as CDSS interventions often automate multiple actions [54,55]. This trial integrated safety measures and their tracking by a nephrologist allowing not only for measurement of safety but also the ability to ensure that any new concerning clinical findings found owing to the trial would be addressed. As previously recommended, it is important to first pilot interventions before widespread implementation to ensure there are no adverse effects in a small population where safety can be more easily assessed [56].

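### The 81.4% reported as Adoption is conditional on opening the advisory, not on its availability as Textbox 1 defines; on the defined base adoption lies between 60.1% and 81.4%, and opt-out among patients offered it is about 14%, not 9.5%

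*Protocol article*

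**What the plan says.** Textbox 1 separates two quantities. The first Adoption outcome is a signed SmartSet out of cases where the BPA was available to the PCP. An Implementation outcome counts orders signed or education given out of cases where the SmartSet was opened. Textbox 1 also lists two Reach outcomes that matter here: the proportion with the BPA available, and the split between high-risk and low-risk CKD.

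The Secondary Outcomes section says the article reports initial results "including all of the Reach outcomes and the first Adoption outcome (PCP SmartSet use").

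The Results then give:

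- PCP BPA Use: "Of the 138 participants with a PCP visit, the BPA was opened for 102 participants (73.9"%).
- SmartSet Use, under the Adoption heading: "Of the 102 participants in which the BPA was opened, orders were signed or patient education was given from the SmartSet for 83 participants", printed as 81.4%.

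The Intervention section gives the trigger rule: "We programmed the eCDSS to trigger the first time that the patient participant visited their PCP after all 3 lab results were available".

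On leaving the study, Recruitment Rate says "55 / 582 patients (9.5%) opted out or withdrew", after 3 further exclusions for deaths. The Abstract says "413 were excluded per protocol and 58 opted out or withdrew". The Intervention section gives 48 opt-outs and 10 later withdrawals. Recruitment and Consent Process says that opt-out letters went to intervention-arm patients and that the study team did not contact usual care patients. Principal Findings cites "low opt-out rates by patients" as a result of the pragmatic design.

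**The concern.** An adoption measure should count a PCP who had the advisory on screen and did not use it. Dividing by opened BPAs removes those cases. Of 138 patients with a qualifying visit, 36 (138 − 102) had no opened BPA, and none of them enters the 81.4%. The number shown under Adoption therefore answers the Implementation question. The two Reach outcomes that would let a reader repair it, BPA availability and the risk split, are not in the Results, although the text says every Reach outcome is reported.

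The opt-out rate has a similar weakness. The usual care arm adds 188 patients to the denominator and, having received no letter, nothing to the numerator.

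Both figures support the feasibility message: high use by providers, low opt-out, and markedly better reach and adoption than earlier studies (Comparison With Previous Work). The article offers its results as a guide for later trials. A planner who took 81.4% as uptake when the tool is available, or 9.5% as refusal among approached patients, could be working with figures that are too favourable.

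**Working it through.** **Inputs.** From the Results: 336 intervention patients; 178 with complete labs; 138 with a PCP visit afterwards; 102 with the BPA opened; 83 with orders signed or education given; 582 patients distributed to three arms; 55 opted out or withdrew; 3 excluded for deaths; final arms 188, 165 and 171. From the Intervention section: labs ordered for 169 and 177 patients after 48 opt-outs, with 10 later withdrawals.

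**1. Reproduce the printed figures.**
- 83/102 = 81.4%
- 102/138 = 73.9%
- 55/582 = 9.45%, printed as 9.5%

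All agree with the article on the denominators it prints.

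**2. Match each rate to its definition.**
- Adoption (Textbox 1): signed ÷ BPA available.
- Implementation (Textbox 1): orders or education ÷ opened.
- Printed under Adoption: 83 ÷ 102 opened. This is the Implementation form.

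**3. Adoption on the defined base.** Under the trigger rule, the BPA should have appeared for all 138 patients with a PCP visit after complete labs. Taking 83 as the number signed:
- 83/138 = 60.1%

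**4. Sensitivity to availability.** A BPA that was opened must have been available, so availability lies between 102 and 138:
- 102 available: 83/102 = 81.4%
- 110 available: 83/110 = 75.5%
- 120 available: 83/120 = 69.2%
- 130 available: 83/130 = 63.8%
- 138 available: 83/138 = 60.1%

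Adoption reaches 81.4% only if the BPA was unavailable in every one of the 36 cases where it was not opened.

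**5. Intervention-arm base for opt-out.** Two sets of counts agree:
- 582 − 188 = 394
- 169 + 177 + 48 = 394

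The final intervention total is 165 + 171 = 336, and 394 − 336 = 58. All post-randomization losses therefore sit in the intervention arms, and usual care is 188 at both points.

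**6. Opt-out or withdrawal among those offered it.**
- 55/394 = 14.0%
- 55/(394 − 3) = 55/391 = 14.1%, with the 3 deaths removed from the base
- 58/394 = 14.7%, on the count in the Abstract and Intervention section

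**7. The two counts.** 48 + 10 = 58 (Intervention), and the Abstract labels all 58 as opted out or withdrawn. Recruitment Rate gives 55 + 3 deaths = 58. The total is the same, but 3 patients carry different labels. The analysed number is unaffected: 582 − 58 = 524.

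**The case against.** The strongest reply is that nothing is miscalculated or hidden. Each percentage is right on its printed denominator, and the whole cascade (53.0%, 77.5%, 73.9%, 81.4%) is in the Abstract, so any reader can form other ratios. That stands: this is a mismatch of label and base, not an arithmetic error.

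A reader might infer that adoption simply is 60.1%. The article does not establish that, for three reasons:

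- Textbox 1 lists a PCP visit after complete labs and BPA availability as separate Reach outcomes, and no availability count is given.
- The Discussion reports unanticipated problems with the eCDSS programming, so the trigger rule does not prove that the advisory appeared for all 138.
- The Intervention section describes a SmartSet only for high-risk patients; low-risk patients had repeat labs queued for signature. Without the risk split, a rate limited to patients who could have a SmartSet signed cannot be computed.

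A reader might also infer that 9.5% breaks a written definition, or that the printed 90.0% participation should be 336/394 = 85.3%. Neither follows. Textbox 1 names a recruitment rate without fixing a denominator, and the 90.0% is labelled as a share of the 582 eligible patients. The case for the intervention-arm base rests on the consent process, not on a breached specification.

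Finally, the Abstract's conclusion refers to use at eligible visits, which 102/138 = 73.9% supports directly. The Discussion also acknowledges that nearly half of the intervention patients never completed the labs. Both points stand. They do not answer the mismatch between the named Adoption outcome and the figure printed for it.

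**Conclusion.** The point holds as a discrepancy between a listed outcome and the result reported for it. The Adoption figure uses the Implementation denominator. On the Textbox 1 base, adoption is 60.1% if the BPA was available for all 138 patients as programmed, and otherwise lies between 60.1% and 81.4%. This takes 83 as the number signed and leaves the risk split aside.

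Opt-out or withdrawal among patients who were offered it is 14.0% to 14.7%, roughly one and a half times the stated 9.5% (14.0/9.5 ≈ 1.5). The range reflects the unreconciled 55 and 58 and the handling of the 3 deaths.

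It would go too far to say that the comparison with earlier work fails. Even 60.1% is above the adoption rates below 50% that the article cites as frequent, so the contrast narrows without reversing. The blood pressure outcome, the power calculation and the intention-to-treat analysis are untouched.

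**What to change.** - Report the number of intervention patients for whom the BPA was available, and the high-risk and low-risk split. Both are listed Reach outcomes that the article says it reports.
- Compute the first Adoption outcome on the availability denominator, and say how low-risk patients, who had no SmartSet described, are treated.
- Move 83/102 = 81.4% to the Implementation heading.
- State opt-out or withdrawal over the intervention-arm patients who were offered it, saying whether the 3 deaths are in the base. The rate over all 582 can stay if it is labelled as such.
- Reconcile the 58 described as opted out or withdrawn (Abstract; 48 + 10 in Intervention) with the 55 plus 3 deaths in Recruitment Rate.
- Temper the adoption comparison in Comparison With Previous Work and the opt-out remark in Principal Findings to match.

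The cost is a text correction plus two counts that the study team should already hold. The downside is that the feasibility figures become less favourable.
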